**Fig. 1 Fig1:**
[figure not shown]
Schedule of enrolment, interventions, and assessments of study

### Participants

In order to be included, patients must be aged 18–55 years, literate, present an IQ score higher than 80, have been diagnosed with bipolar I or II based on Structured Interview for DMS IV (SCID) [27], and be in full or partial remission according to the DSM IV [28]. Exclusion criteria are: presence of substance or alcohol abuse in the last six months; current suicide risk; organic mental disorders; or scores higher than 12 in the Montgomery-Åsberg Depression Rating Scale (MADRS) or the Young Mania Rating Scale (YMRS) at the beginning of the intervention [28].

Recruiting will take place at an outpatient service provided by the Bipolar Disorder Research Program (PROMAN) at the University of São Paulo Medical School, Brazil. Patients will receive invitations individually and sign an informed consent. This research was approved by an internal ethical committee and registered in ClinicalTrials.gov: NCT02766361.

### Procedure and outcomes

Once included, patients will complete the Portuguese versions of the following self-report questionnaires:Abbreviated instrument of quality of life (WHOQOL-bref) [29]: evaluating quality of life scored in four domains: physical, psychological social, and environmentalBarratt Impulsiveness Scale 11 (BIS 11) [30]: assessing the personality/behavioral construct of impulsiveness. It includes 30 items describing common impulsive or non-impulsive behaviors and preferencesSocial Skills Inventory (IHS) [31]: self-report instrument assessing social skills. It consists of 38 items, each describing a situation of interpersonal relationship and a demand for ability to react to that situationBiological Rhythms Interview of Assessment in Neuropsychiatry (BRIAN) [32]: consisting of 21 items divided into five main areas related to circadian rhythm disturbances in psychiatric patients, including sleep, activities, social rhythms, eating patterns, and predominant rhythmFunctioning Assessment Short Test (FAST) [33]: a 24-item interview assessing functional impairments in BD, and including autonomy, occupational functioning, cognitive, financial issues, interpersonal relationships, and leisure timeKnowledge about Affective Disorders Interview (KADI): brief questionnaire evaluating the patient’s knowledge about prognostic, medication, etiology, symptoms, and diagnosis of BD [34]

A brief neuropsychological battery will be conducted, which includes two subtests of matrix reasoning and vocabulary from the Wechsler Abbreviated Scale of Intelligence (WASI) [35] and following subtests from the Cambridge Neuropsychological Test Automated Battery (CANTAB): Motor Screening Task (MOT); Rapid Visual Information Processing (RVP); Reaction Time (RTI); Spatial Span (SSP); Spatial Working Memory (SWM); One Touch Stockings of Cambridge (OTS); Pattern Recognition Memory (PRM); Delayed Matching to Sample (DMS); Attention Switching Task (AST); and Emotion Recognition Task (ERT).

Participants will also complete the initial assessment and mood module of the Structured Clinical Interview for DSM-IV (SCID-IV) [36] at week 12 after inclusion into the study and 12 months thereafter.

## Interventions

### Treatment as usual (TAU)

The control group from this study will receive standard outpatient treatment offered in our clinic, which involves psychopharmacological mood stabilization and regular contacts with mental health nurses. The type and dosage of pharmacological treatment will follow the physician decision, respecting individual demands. All pharmacological treatment will be monitored and recorded in accordance to the Litmus study [26].

### Cognitive Behavioral Rehabilitation (CBR)

We developed a 12-session intervention combining previous experience in cognitive behavior therapy for bipolar patients [14] with several elements of cognitive remediation. The first step was to identify behaviors that have an important role in patients’ autonomy, followed by determining which cognitive domains are involved. The core objective was to promote the generalization of the learnt behaviors in the daily routine. Described below is the arrangement of each session, divided into three major modules.

The first module comprises four sessions attempting to improve attention and memory, considering the necessity to retain the information discussed throughout the sessions. There are two target behaviors involved: adherence to pharmacological treatment and mood monitoring. The cognitive remediation exercises seek to enhance verbal and visual memories, while secondarily enhancing attention with the paper material included in the manual. In the first session, group members and psychotherapists introduce themselves, followed by a discussion regarding the manual, individual’s expectations, and the importance of attendance. The second session explores the concept of attention and its importance as a door to further cognitive functions; the group also learns exercises aimed at training attention and memory. The third session focuses on medication adherence and its relation to attention. The core of the third session is the organization of the patient’s environment, which is frequently chaotic; a discussion about cues is encouraged at the end of the session. The fourth session starts by introducing mood graphics to patients and the importance of the early identifying of mood episodes. At the end of the first module, patients are encouraged to cook as a method of reinforcing what they have learned while enhancing their autonomy.

The second module targets social cognition and communication. The fifth session familiarizes the patients with the concept of automatic thoughts [37] and a guide to identify its presence. Cognitive distortions are discussed along with examples provided by the participants’ own experiences. The sixth session begins returning to the initial theme by habituating patients to the automatic thought record [38]; patients are stimulated to restructure their own thoughts during experiences identified in previous sessions. Mental flexibility and empathy are introduced and discussed. The seventh session acquaints patients with assertive communication and emotion recognition by teaching role-playing exercises and the importance of positive assertiveness. The eighth session follows the same agenda as the seventh.

The last module of CBR aims at problem-solving strategies and relapse prevention. The ninth session begins with the identification of personal problems, mainly by distinguishing it from preoccupations; the topic is important because patients often incorporate their problems to expectations and desires, generating an urge to abandon them. The session ends by emphasizing the importance of mental flexibility in generating as many responses as possible to each identified problem. In the tenth session, patients learn solving-problem techniques in a systematic setting. The 11th session is devoted to reviewing information and clarifying possible doubts from the patients; patients are also encouraged to debate the importance of regular routines and regular sleep, which can be adjusted using sleep hygiene techniques. A progressive muscle relaxation ends the session. Finally, the last session’s target is to avoid future mood relapses, by returning to the personal goals defined in the first session and prompting patients to develop a prevention plan. The acronym H.U.M.O.R. resumes the core points of the post-intervention maintenance program: (1) Habituate to a regular routine; (2) Use what you have learnt; (3) Monitor your mood; (4) Observe arising problems and deal effectively with it; and (5) Respond to automatic thoughts. All patients in the CBR group will also receive TAU.

## Statistical analysis

### Sample size

The sample size calculation was based on the proportion of patients that remain episode-free after 12 months following a group intervention. Previous studies utilizing TAU exhibited a decrease of bipolar relapses in 30% of patients after a one-year follow-up [39]. The present study anticipates a 55% success rate in prevention of mood relapses, during the same period, in patients assigned to the CBR. Thus, considering an 80% power to obtain a 5% significance, an estimated sample of 28 individuals per group, 56 in total, should be sufficient to achieve significant results. A previous study conducted by the same research team [14] measured a drop-out rate of 10% in a one-year follow-up. For this latter reason, the study will consist of 60 participants.

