### Baseline and follow-up data

In order to measure the effectiveness of the intervention, the study will employ the following statistical tests: (1) Chi-squared and Mann–Whitney to test homogeneity between the groups at the beginning of the interventions; (2) Student’s t-test or Mann–Whitney to investigate the effects of such interventions, pre and post treatment, depending on the distribution of the data; (3) an analysis of variance, with and without adjustment for mood symptoms scores, IQ and BD duration, for comparison between groups; and (4) the Kaplan–Meyer survival method with log rank test for statistical analysis, to investigate the survival data between groups, which measures in weeks, the time to the first episode as an event. To be considered as an intervention completer, patients assigned to CBR should attend at least eight sessions (66.7%). Intent to treat analyses will be conducted in order to include all available data and missing data will be handled accordingly to the SPIRIT checklist recommendations (Additional file 1).

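### 28 per group does not give 80% power for 55% versus 30% episode-free; two-sided power is about 47–51%, and the drop-out allowance is also short

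*Protocol article*

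**What the plan says.** The Sample size section sizes the trial on a binary quantity: "The sample size calculation was based on the proportion of patients that remain episode-free after 12 months following a group intervention". For the control arm it says: "Previous studies utilizing TAU exhibited a decrease of bipolar relapses in 30% of patients after a one-year follow-up". For the intervention: "The present study anticipates a 55% success rate in prevention of mood relapses, during the same period, in patients assigned to the CBR". It then concludes: "considering an 80% power to obtain a 5% significance, an estimated sample of 28 individuals per group, 56 in total, should be sufficient". It cites a 10% one-year drop-out from the team's earlier study and sets enrolment at 60.

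The Methods/Design section describes random assignment to two arms, CBR and TAU. The primary outcome is time in weeks to the first episode, and Baseline and follow-up data names the test: "the Kaplan–Meyer survival method with log rank test for statistical analysis, to investigate the survival data between groups". The article gives no formula, no software and no sidedness for the calculation.

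**The concern.** A 25-point difference between two randomised proportions near the middle of the scale usually needs more than 28 per arm for 80% power. Because the rates, significance level, power and resulting number are all printed, this can be checked directly and does not depend on a fuller protocol or an analysis plan.

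The calculation supports the primary outcome. If the stated power is wrong, the trial can miss significance far more often than the claimed one time in five, even when CBR works exactly as assumed. Anyone weighing a non-significant result against a stated 80% power would then give it too much weight as evidence against CBR.

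**Working it through.** **Inputs (Sample size section).** TAU 0.30, CBR 0.55, difference 0.25, significance 5%, power 80%, 28 per group, drop-out 10%, enrolment 60. The 30% is loosely worded and is read here as the TAU episode-free proportion. Sidedness is not stated, so both are shown. Normal quantiles: 1.960 (two-sided 5%), 1.645 (one-sided 5%), 0.8416 (80% power). (1.960 + 0.8416)² = 7.849.

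**1. What reproduces 28.** A one-sample test of 55% against a known 30%, two-sided:

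n = [1.960·√(0.30·0.70) + 0.8416·√(0.55·0.45)]² / 0.25² = (0.898 + 0.419)² / 0.0625 = 27.75, rounded up to **28**.

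This treats the TAU rate as free of sampling error.

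**2. Two proportions, two arms, two-sided.**
- Unpooled: 7.849 × (0.21 + 0.2475) / 0.0625 = 57.5, so **58 per arm**.
- Pooled (mean rate 0.425): [1.960·√(2·0.425·0.575) + 0.8416·√0.4575]² / 0.0625 = (1.370 + 0.569)² / 0.0625 = 60.2, so **61 per arm**.
- One-sided: 45.3 unpooled and 47.3 pooled, so 46–48 per arm.

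**3. Log-rank, the planned test.** The article states no hazard ratio. Under proportional hazards the two 12-month proportions imply HR = ln 0.55 / ln 0.30 = 0.497.
- Schoenfeld: 4 × 7.849 / (ln 0.497)² = 64.06, so **65 events**. Expected events per pair of patients are 0.70 + 0.45 = 1.15. This gives 64.06/1.15 = 55.7 to 65/1.15 = 56.5, or **56–57 per arm**.
- Freedman's formula: 70 events, 61 per arm.
- One-sided: about 44 (Schoenfeld) to 48 (Freedman) per arm.

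**4. Power at the planned size.** For proportions, the pooled formula is inverted. At 28 per arm, (0.25·√28 − 1.370)/0.676 = −0.070, giving 47.2%. For log-rank (Schoenfeld), 28 × 1.15 = 32.2 events and √32.2/2 × 0.700 − 1.960 = 0.026, giving 51.0%.

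| Per arm | Proportions, two-sided | Log-rank, two-sided | Proportions, one-sided | Log-rank, one-sided |
|---|---|---|---|---|
| 27 (60 less 10%) | 45.8% | 49.6% | 58.7% | 62.0% |
| 28 (as stated) | 47.2% | 51.0% | 60.1% | 63.4% |
| 30 (no losses) | 49.9% | 53.8% | 62.7% | 66.0% |

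The Freedman approximation for log-rank gives 46.6%, 48.0% and 50.6% two-sided, inside the same range. Fisher's exact test at 28 per arm has about 36% power.

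**5. Detectable difference.** With TAU at 30%, two-sided 5% and 80% power, the CBR rate that can be detected is about 64% (log-rank, Schoenfeld) to 65% (pooled proportions) at 30 per arm. At 27 per arm it is about 66% to 67%.

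**6. Drop-out.** 60 × 0.90 = 54, or 27 per arm, below the stated 56. To retain 56, enrolment would have to be 56 / 0.90 = 62.2, so 63.

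**The case against.** **The cause is not documented.** A reader might infer that the sponsor used a one-sample formula. The article does not say so. The match is close, but an input slip would also land there: 30% versus 67% in a two-arm formula gives 28 per group. This objection stands, so the one-sample origin is only a likely explanation. The shortfall does not depend on it.

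**Sidedness is not stated.** A reader might take the roughly 50% power as unconditional. It holds only for a two-sided test, the usual default. With a one-sided test, power is 59–66%. That qualification stands, but 80% is not reached on either reading.

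**The 30% is loosely worded.** Reading both rates as relapse rates (70% versus 45%) gives the same sample size. Inverting only one of them narrows the gap to 15 points and requires about 163 per arm, which worsens the shortfall.

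**Censored patients still contribute to a log-rank test.** Correct. Treating all drop-outs as absent (27 per arm) is pessimistic, and assuming no losses (30 per arm) is optimistic. The log-rank power lies between about 50% and 54%.

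**The trial is described as proof-of-concept.** The Limitations section uses that label and calls for larger multicentre work if CBR proves beneficial. This softens the consequences but does not withdraw the 80% claim. A reader might also infer that the sponsor intends to read a null result as showing that CBR does not prevent episodes. The article says no such thing, and that remains only a risk of misreading.

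**Conclusion.** The stated power is wrong as written. With the article's own rates, 28 per group is about half of what a two-sided two-arm comparison requires (56–61 per arm) and well below the one-sided requirement (about 44–48). Two-sided power is about 47–51% at 28 per arm, and 46–54% over the range from 27 per arm to 30 per arm. One-sided power over that range is about 59–66%.

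The conclusion rests on reading 30% and 55% as 12-month episode-free proportions with 1:1 allocation and, for the log-rank figures only, on proportional hazards. It does not rest on how the figure of 28 arose. The drop-out step is a second, smaller error in the same paragraph. Neither error shows that the trial is invalid or must enrol more patients. They show that its stated power cannot be relied on.

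**What to change.** Keep the 60 patients and replace the power sentence in the Sample size section with text such as:

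> With 60 randomised and 10% drop-out, the trial has about 46–54% power (two-sided 5%) for 55% versus 30% episode-free at 12 months. 80% power would need about 65 events, or 56–61 evaluable patients per arm. The difference detectable with 80% power is about 64–67% versus 30%.

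State the sidedness and the formula used. Correct the drop-out step: either say that 60 enrolled leaves about 54 evaluable, or note that retaining 56 would take 63.

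As an optional addition, say in advance that a non-significant log-rank test will not be read as absence of effect. That fits the proof-of-concept description in Limitations, but it is a reporting choice and not part of the arithmetic correction.

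The cost is a text change and a less favourable stated power. No patients, visits or analyses are added. The Trial status section reports 40 patients included and the study underway, so the statement can still be corrected before the results are read.

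### Sixty participants do not cover the stated 10% drop-out from 56: about 54 would remain, a small shortfall in the protocol's own arithmetic

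*Protocol article*

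**What the plan says.** All the figures stand in one paragraph of the protocol article, under Statistical analysis, Sample size.

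- The trial is sized on the proportion of patients still episode-free at 12 months. For TAU the text says "Previous studies utilizing TAU exhibited a decrease of bipolar relapses in 30% of patients after a one-year follow-up", which I read as 30% episode-free. For CBR, "The present study anticipates a 55% success rate in prevention of mood relapses".
- The design target is stated as "considering an 80% power to obtain a 5% significance". Whether the 5% is one- or two-sided is not stated.
- The result is "an estimated sample of 28 individuals per group, 56 in total, should be sufficient to achieve significant results".
- An earlier study by the same team "measured a drop-out rate of 10% in a one-year follow-up. For this latter reason, the study will consist of 60 participants".

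No other allowance for loss is given. Under Baseline and follow-up data, the article plans intention-to-treat analyses using all available data, and a Kaplan-Meier analysis with a log-rank test of time in weeks to the first episode.

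**The concern.** The paragraph ties 60 to the 10% drop-out and to nothing else, so a reader takes it as the 56 protected against that loss. If 10% are lost, fewer than 56 remain. The enrolment total then contradicts the reason given for it, and the power statement attached to 56 no longer describes the sample the trial expects to have at 12 months. The outcome at stake is the primary one, so a null result would be read against this statement.

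**Working it through.** **Inputs** (all from Sample size): 56 patients needed, 28 per group; drop-out 10% over one year; 60 enrolled; 30% and 55% episode-free at 12 months. Equal allocation is inferred from the equal group sizes. Two-sided 5% is my assumption.

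**1. Can the plan's 60 be reproduced?** Neither usual rule gives it.
- Division by the retained fraction: 56 / (1 - 0.10) = 62.2, so 63. Rounding up within each arm: 28 / 0.90 = 31.1, so 32 per arm, 64 in total.
- The cruder shortcut of adding 10%: 56 x 1.10 = 61.6, so 62.

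**2. What does 60 deliver?**
- Remaining after 10% loss: 60 x 0.90 = 54, or 27 per arm, two short of 56.
- Largest loss that still leaves 56: 1 - 56/60 = 4/60 = 6.7%.
- Check on the alternatives: 63 x 0.90 = 56.7 and 64 x 0.90 = 57.6, both at or above 56.

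**3. Effect on the 12-month comparison of proportions.** With p1 = 0.30, p2 = 0.55 and mean p = 0.425, the usual normal approximation is

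power = Phi{ [0.25 x sqrt(n) - 1.96 x sqrt(2 x 0.425 x 0.575)] / sqrt(0.30 x 0.70 + 0.55 x 0.45) }.

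- n = 28 per arm: 47.2%.
- n = 27 per arm: 45.8%.
- Difference: 1.4 percentage points.

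**4. Effect on the planned log-rank test.** Here a drop-out is censored and contributes follow-up until leaving. Under proportional hazards the hazard ratio is ln 0.55 / ln 0.30 = 0.50. Expected 12-month event probabilities are 0.70 and 0.45, on average 0.575. Power by the Schoenfeld formula is Phi{ sqrt(events) x |ln HR| / 2 - 1.96 }. The article gives no timing of loss, so I show a range.

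| Scenario | Expected events | Power |
|---|---|---|
| 56, all followed for 12 months | 56 x 0.575 = 32.2 | 51% |
| 60 enrolled, 6 lost on day 0 | 54 x 0.575 = 31.1 | 50% |
| 60 enrolled, 6 lost uniformly over the year | 31.05 + 2.0 = about 33.0 | 52% |
| 60 enrolled, 6 lost only at the very end | 60 x 0.575 = 34.5 | 54% |

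The 2.0 extra events in the third row assume exponential times to episode fitted to 30% and 55%. A patient with a uniform leaving time then has an event first with probability 0.42 (TAU) or 0.25 (CBR), and 3 x 0.42 + 3 x 0.25 = 2.0.

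**The case against.** The strongest reply is that the primary analysis does not discard drop-outs. Under intention to treat with a log-rank test they are censored, so 60 enrolled does not shrink to 54 for that test. This stands: with losses spread evenly over the year, 60 enrolled yields about as many events as 56 fully followed, or slightly more. A reader might infer that the slip pushes the power of the primary test down further. The documents do not support that, because it would require nearly all the loss to come very early, and the article says nothing about its timing.

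The reply does not rescue the figure itself. The calculation was made for a 12-month proportion, which needs 12-month status, and the authors chose to enlarge the sample for drop-out. If censoring made enlargement unnecessary, then the reason given for 60 is wrong instead.

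Two other objections are fair. The shortfall is only two patients. And 28 per group is itself far too low: with 30% against 55%, 80% power and two-sided 5%, a two-group comparison needs 58 (unpooled variance) to 61 (pooled) per group. A reader might therefore cite power near 46% as the size of the drop-out error, or expect 63 or 64 patients to restore 80%. Neither follows. Power is already 47.2% at 28 per group, and keeping 56 after loss merely returns it to that level.

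**Conclusion.** The point holds as an arithmetic inconsistency of small effect. On the protocol's own figures, 60 enrolled leaves 54 with known 12-month status against a stated 56; the matching enrolment is 63, or 64 with equal arms. Nothing else in the article corrects this.

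Its separate cost is about 1.4 power points for the 12-month proportion. For the log-rank test it runs from about 1 event (roughly 1 to 1.5 points) if every drop-out leaves on day 0, to no loss at all if drop-out is uniform. These sizes assume two-sided 5%, 1:1 allocation, 30% read as the TAU episode-free rate and, for the log-rank range, proportional hazards; the uniform-loss row also assumes exponential times. The counts of 54, 63 and 64 depend on none of these beyond 1:1 allocation. The distance from 80% power belongs to the base sample size.

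**What to change.** Replace the closing statement on 60 participants with one that says: 60 randomised with 10% loss gives about 54 patients (27 per arm) with known 12-month status. Quote the power at that number and, for the log-rank test, the assumed timing of loss. Use a term such as known 12-month status rather than completers, because the article already defines an intervention completer as a CBR patient attending at least eight sessions.

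When the base size is corrected, divide the new figure by 0.90. For instance, 61 per group would become 61 / 0.90 = 67.8, so 68 per group. If 56 is kept in the text, the consistent enrolment is 63 (64 for equal arms), with a note that this does not bring power to 80%.

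The restatement costs one sentence, changes nothing in design or conduct, and makes the reported figure slightly less favourable. Trial status reports 40 patients included, so the target had not yet been reached when the article was written.
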